## Abstract

Concerning numbers of childhood behavior problems have been reported worldwide. Parenting interventions are considered one of the most effective early strategies to intervene with externalizing conduct. This protocol outlines a feasibility RCT that aims to implement a parenting intervention in Portugal and (a) test key feasibility parameters, (b) assess the fidelity and acceptability of the program, and (c) explore its effectiveness in childhood behavior problems, parenting skills, parental concern, and parental sense of competence. A double-blinded, two-arm feasibility RCT is described. The participants are the primary caregivers of children between the ages of two and eleven years old that identify difficulties in managing their child’s behavior. Families will be randomly assigned to an intervention arm and a waitlist control arm. Parents in the intervention arm will participate in the Being a Parent program (Portuguese version: Ser Pai & Ser Mãe), an eight-week group intervention. Outcomes will be assessed using quantitative and qualitative measures throughout three assessment periods (pre- and post-intervention, and follow-up). This study marks the first feasibility RCT of the Being a Parent program outside the UK. The findings will provide information on the global strength of this program. Challenges and clinical implications are also discussed.

## 1. Introduction

Worldwide prevalences present concerning numbers of childhood behavioral problems [1,2,3,4]. In most cases, these difficulties may arise as a child’s response to coping with multisystemic strains (e.g., adverse childhood experiences) and/or as the first signs of early diagnosis of emotional and behavioral disorders, such as Conduct Disorders (CDs). Simultaneously, they often manifest as predictors of youth’s future social, physical, and mental health issues and are especially linked to adverse outcomes such as school dropout, substance abuse, and criminal offending [5,6,7].

In this context, many stakeholders have been working extensively to globally counteract childhood behavior problems and, consequently, the onset of a lifetime pathway of psychosocial maladjustment. The current empirical evidence strongly suggests that parenting interventions are one of the most cost-effective strategies to prevent and intervene with childhood behavior problems [8,9,10]. Their versatility and applicability across various developmental stages allow for the enhancement of parent–child relationships and the promotion of short- and long-term outcomes [11].

Consequently, it is no surprise that many international organizations [12] recommend the dissemination of evidence-based parenting programs around the globe. Taking into account that creating an intervention from scratch can have several associated costs [13], transporting evidence-based programs to other countries can be one of the most viable solutions for providing a cost-effective strategy to families. In fact, two recent meta-analyses examined the effectiveness of disseminating parenting interventions to other cultural contexts and concluded that interventions can still be effective, even when transported to rather different cultural backgrounds [14,15].

This may be the case for Portugal. Following international trends, cases of childhood behavior problems in Portugal have been consistently rising. In 2023, 17% of cases reported by Portuguese Child Protective Services [16] were related to behavioral problems, such as defiance, aggression, hyperactivity, difficulty following instructions and rules, and challenges in emotional regulation. However, to our knowledge, many Portuguese services do not have any evidence-based responses with which to effectively intervene. Thus, it is critical to provide Portuguese services with an empirical tool that can aid practitioners.

The Being a Parent (Portuguese version: Ser Pai & Ser Mãe) program is an evidence-based parenting program developed in the United Kingdom (UK). It has many advantages, mainly associated with it being a peer-led, brief, group intervention with highly cost-effective results [17]. A significant body of research supports the effectiveness of the Being a Parent program in addressing childhood behavioral issues. It has been extensively evaluated in the UK [18,19] and has also been implemented and assessed in Australia [20], with both evaluations demonstrating promising outcomes in reducing externalizing behaviors and enhancing parental well-being. Furthermore, independent organizations in both the UK and Australia have rated the *Being a Parent* program as an effective and cost-efficient parenting intervention [17,21]. In fact, a meta-analysis from Piquero et al. [22] that compared the Being a Parent intervention with similar interventions currently available suggests that it is one of the most effective group interventions for reducing disruptive behavior and improving positive parenting skills. This effectiveness may stem from its peer-led delivery model, which promotes relatability and trust among participants. Additionally, its content is grounded in the most evidence-based and effective methodologies (e.g., attachment approaches) for group-based parenting interventions targeting childhood behavior problems. A key strength of the program is also its emphasis on parental self-care, equipping parents with tools to enhance their own well-being alongside improving their parenting skills.

Implementing an evidence-based group parenting program, such as the Being a Parent program, in Portugal can have various benefits. Firstly, this program equips parents with practical, evidence-based parenting strategies that promote positive behavior and emotional regulation in children, by promoting strong parent–child relationships, setting clear boundaries, and using positive reinforcement, which are essential tools for managing and reducing behavioral issues [18]. By also focusing on parent self-care, the program helps reduce parental stress and enhances their ability to manage challenging behaviors effectively [18]. Hence, it can address behavior problems in children at an early stage, thus preventing the escalation of externalizing difficulties and reducing the likelihood of more severe problems in the future. Moreover, the positive effects of the Being a Parent program extend beyond families and can impact communities overall, as seen in the national scaling study from Day et al. [19]. Finally, this program is considered a cost-effective tool, making it feasible for implementation in service settings.

Notwithstanding the aforementioned findings, many questions arise from the practicability of effectively implementing the Being a Parent program in Portugal. Indeed, there are substantial contextual disparities between Anglosphere and non-Anglosphere countries, like the UK and Portugal. Consequently, there is a need for a systematic adaptation of the Being a Parent program to take into account linguistic, legal, and cultural factors compatible with the cultural patterns, meanings, and values distinctive to Portugal [23]. For example, one main difference from the UK context concerns the practice of psychology. In Portugal, the practice of psychological acts is regulated and exclusively entrusted to licensed psychologists, limiting the possibility of implementing peer-led approaches. Thus, changes regarding the delivery of the program will have to be executed to adapt the intervention to the Portuguese legal context.

Moreover, it is important to take into consideration that very few evidence-based parenting interventions have been tested in Portugal, and thus, the feasibility of implementing an evidence-based parenting program, such as the Being a Parent program, raises relevant, unanswered questions pertaining to acceptability, feasibility, and effectiveness. Indeed, the acceptability of these types of programs by Portuguese parents, as well as their subjective experiences, have yet to be thoroughly explored. Therefore, it becomes imperative to gain empirical knowledge of these crucial aspects prior to committing to a comprehensive trial. In this sense, conducting a feasibility study is key for the exploration of the impact of cultural differences and parents’ adherence and acceptability, and for the refinement of a subsequent large-scale randomized controlled trial (RCT). Feasibility studies allow practitioners to uncover implementation issues, address uncertainties related to trial methodologies, and assess the initial effects of an intervention [24].

Thus, this paper outlines the methodology and procedures of a feasibility RCT that aims to test the potential impact of the Being a Parent program in the Portuguese context. Our goals are four-fold: (a) to analyze key feasibility parameters (such as adherence and retention); (b) to assess the fidelity and acceptability of the Portuguese version of the Being a Parent program; (c) to explore the effectiveness of the program in childhood behavior problems; and (d) to explore the effectiveness of the program in parenting skills, parental concern, and parental sense of competence.

## 2. Materials and Methods

The Being a Parent parenting program will be tested in Portugal using a two-arm parallel-group feasibility RCT. The following section describes the design, participants, and methodology of this study.

### 2.1. Design

This is a two-arm parallel-group feasibility RCT, in which families will be randomly assigned to an intervention arm and a waitlist control arm, with a 1:1 allocation ratio. Parents in the intervention group will participate in the Being a Parent program, while the waitlist control group will not receive any intervention during this phase but will be given the opportunity to participate in the program after post-intervention assessments are conducted. Two outcome assessments will be completed by both arms at baseline and post-intervention, and an additional 6-month follow-up will be conducted only with the intervention arm, as assessing the control group at this stage would not provide accurate control data for comparison since the control group will have been participating in the Being a Parent program. Concurrently, a qualitative process assessment will be performed using semi-structured interviews to thoroughly explore the experience of the families who participated in the Being a Parent program, independently of their designated trial group. Figure 1 summarizes the participant flow throughout the study. As illustrated, parents will be recruited through different channels and will be asked to sign in through our website. If included in the study, participants will complete baseline assessments and proceed to randomization to either an intervention group or a control group. Post-intervention assessments will be completed by both groups, and the intervention group will have an additional 6-month assessment. Qualitative assessments will also be conducted.

### 2.2. Participants and Eligibility

The participants will be primary caregivers from the district of Lisbon or Setúbal (Portugal) with a child between the ages of 2 and 11 years old. One or both parents can choose to participate. Families will be eligible for inclusion if a parent identifies difficulties in managing the child’s behavior. Since the Being a Parent program is designed to improve parenting skills for the management of behavioral issues, as long as parents are struggling with child behavior, they are likely to find the intervention helpful. As exclusion criteria, the following principles were defined: (a) families where the index child is in foster care or in an adoption process at the time of the study, as such children are not cohabiting with their parents; (b) parents of children with severe neurodevelopmental problems (such as autism), as children with neurodevelopmental disabilities often require specialized interventions; and (c) parents who are engaged in another structured parenting intervention; and (d) parents who are unable to read or write Portuguese.

### 2.3. Procedures

#### 2.3.1. Recruitment

Participants will be recruited through four main channels, namely, (1) social media, (2) primary schools and children’s centers, (3) social services and child protective services, and (4) health centers, such as hospitals. Prospective parents will be directed to the study’s website for more information and will have access to an online registration survey where they can formalize their interest and sign in. Since both parents from a family unit can participate, when the first parent (Parent 1) registers, they may convey the interest of their co-parent (Parent 2) in participating and provide their details. Subsequently, the research team will contact Parent 2 to officialize their registration.

Following the completion of the registration form, the research team will assess eligibility. Those deemed ineligible will be promptly communicated with and informed of other available community resources. Eligible caregivers will be notified of their eligibility via e-mail, and two weeks before the beginning of the parenting program, they will be asked to complete consent forms and baseline measures, also through an online survey, to formalize their participation in the study. Informed consent will be provided by checking a box in the survey acknowledging that parents have read all the information and agree to participate.

#### 2.3.2. Randomization

The randomization of participants will occur after the collection of baseline data and will be conducted only by one researcher, assuring that the rest of the research team will be blinded to randomization. Participants will be randomly assigned to either the intervention group or the waitlist control group using block randomization to ensure balanced allocation across key variables that could influence the study outcomes. Blocks will be created using Random Allocation Software (version 2.0) and will be based on four stratification variables: child’s age (categorized into predefined age ranges to account for developmental differences), child’s sex (male or female, as behavioral outcomes may vary by gender), socioeconomic status (SES; classified into low, medium, or high, based on parental education), and whether one or both parents of a family unit will participate. Within each block, participants will be randomly assigned to groups using a computer-generated randomization sequence, ensuring equal distribution across intervention and control groups. This approach will minimize confounds by balancing critical baseline characteristics and will enhance the internal validity of the study [25]. Additionally, to ensure transparency and replicability, the randomization sequence and its implementation will be documented in detail and securely stored for auditing purposes.

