### 2.7. Sample Size

Sample size calculation was based on the CONSORT 2010 statement extended to feasibility trials [35] and the Lewis et al. [36] methodology. This approach calculates sample size by conducting hypothesis testing based on estimations of predefined feasibility outcomes being within the unacceptable “red zone” (null hypothesis) and contrasting this with an alternative hypothesis of being within the “favorable” green zone [35]. A sample size is considered appropriate if it allows for ≥80% power to reject being in the red zone if the green zone holds true. For detailed information about this methodology, please consult Lewis et al. [36].

Progression parameters and their subsequent point estimates as described in Table 2 were used. Considering a one-tailed, one-sample binomial test based on normal approximation (with continuity correction) with α = 0.05, the following minimum sample sizes for each parameter were obtained:Feasibility of participant retention at post-intervention (Rul = 0.50 and Gll = 0.70)—41 participantsFeasibility of consent rate (Rul = 0.40 and Gll = 0.60)—42 participantsFeasibility of program completion (Rul = 0.45 and Gll = 0.75)—18 participants (intervention arm)Feasibility of program acceptability (Rul = 0.45 and Gll = 0.75)—19 participants (intervention arm)Feasibility of program fidelity (Rul = 0.40 and Gll = 0.70)—19 participants (intervention arm)

Therefore, a sample size of 42 participants, with 25 participants in the intervention arm, allows for ≥80% power to reject the null hypothesis for each of the feasibility outcomes. Moreover, this sample size is sufficient for the estimation of effect sizes for a future larger trial, as it allows for the collection of preliminary data needed to calculate reliable effect size estimates and assess the variability in psychological measures.

Regarding our qualitative data, according to the recommendations of Boddy [37] and van Risjnsoever [38], we aim to recruit 10 to 12 participants, as this sample size is often sufficient to achieve data saturation when the aim is to explore shared experiences within a relatively homogeneous group. Moreover, we will closely monitor data saturation during analysis and will adjust the sample size if necessary to ensure robust and meaningful findings.

**Table 2 healthcare-13-00176-t002:** Feasibility progression parameters.

Parameter	Thresholds		Justification

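### Blocking within four stratification variables gives at least 24 strata for about 42 families, so the stated equal distribution between arms is not ensured

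*Protocol article*

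**What the plan says.** Protocol article, section 2.1 (Design): "families will be randomly assigned to an intervention arm and a waitlist control arm, with a 1:1 allocation ratio".

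Section 2.3.2 (Randomization) describes the method as "using block randomization to ensure balanced allocation across key variables that could influence the study outcomes". On how the blocks are formed, the same section states: "Blocks will be created using Random Allocation Software (version 2.0) and will be based on four stratification variables". The variables and their levels are:

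- SES, in three levels, "classified into low, medium, or high, based on parental education"
- participation by one parent or by both, so two levels
- sex of the child, two levels
- age of the child, with the number of levels not given: "categorized into predefined age ranges to account for developmental differences".

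A computer-generated sequence then allocates within each block, which the article describes as "ensuring equal distribution across intervention and control groups".

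Section 2.7 (Sample Size) arrives at "a sample size of 42 participants". The article does not mention minimisation, merging of sparse strata or a limit on overall imbalance.

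**The concern.** Stratified blocking controls arm sizes only where strata are large enough to fill blocks. A stratum with an odd count cannot split equally, and a block left unfilled at the end of recruitment guarantees nothing. When strata are nearly as numerous as families, the leftovers add up across strata and the scheme moves toward simple randomisation. Section 2.3.2 states the opposite as a property of the design.

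Two things are at stake. The article claims a property that the scheme does not have. The trial is also meant to inform a full RCT, which could inherit the scheme. The stratification was intended to balance four factors as well, so the check asks both how far arm sizes drift and how much factor balance is gained.

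**Working it through.** **The plan's own figure.** Section 2.7's total comes from the consent-rate parameter, 0.40 v 0.60, one-sided α = 0.05, power 80%, with continuity correction.

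- Uncorrected: n = [(1.645·√0.24 + 0.842·√0.24)/0.20]² = 37.10.
- Corrected: (37.10/4)·[1 + √(1 + 2/(37.10·0.20))]² = 41.95, so 42. The stated 42 reproduces.

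**Number of strata.** The plural age ranges means at least two levels.

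- Two age ranges: 2 × 2 × 3 × 2 = 24 strata, and 42/24 = 1.75 families per stratum.
- Three age ranges: 3 × 2 × 3 × 2 = 36 strata, and 42/36 = 1.17 per stratum.

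Section 2.7 counts participants, whereas section 2.1 randomises families. If the 42 include second parents, there are fewer families and the strata are sparser.

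**How full the strata are.** With 24 equally likely strata and 42 families, about 20 are occupied, about 7 hold one family and about 12 hold an odd number. With blocks of 4, about 32 of the 42 families sit in strata that never fill a block. With blocks of 6, about 41 do.

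**Arm-size difference.** Monte Carlo, 10,000 trials per row, 42 families, a separate permuted-block list per stratum. The article does not give the factor shares, the number of age ranges or the block size, so these are assumptions: sex 60/40, SES 20/35/45, one/both parents 65/35, age 50/50 or 35/40/25, blocks of 2, 4 and 6.

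| Strata | Block | SD of difference | Exactly 21:21 | Difference ≥ 6 |
|---|---|---|---|---|
| 24 | 2 | 3.3 | 23% | 13% |
| 24 | 4 | 4.3 | 19% | 24% |
| 24 | 6 | 5.0 | 16% | 32% |
| 36 | 2 | 3.9 | 21% | 20% |
| 36 | 4 | 4.9 | 16% | 30% |
| 36 | 6 | 5.5 | 14% | 36% |
| Simple randomisation | – | 6.5 | 12% | 44% |

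Changing the parent split to 60/40 with equal age bands moves these by a point or two. Equally likely strata give 14–21%, 26–33% and 34–38% in the last column for blocks of 2, 4 and 6.

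A hand check for blocks of 2 and 24 equally likely strata: each odd stratum contributes ±1, so the SD is about √11.7 = 3.4, against 3.4 simulated.

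**Factor balance.** SD of the arm difference within one level of an evenly split two-level factor (about 21 families), 24 equally likely strata:

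- stratified blocks of 2, 4, 6: 2.4, 3.2, 3.7
- unstratified 21:21: 2·√(21·¼·21/41) = 3.3
- simple randomisation: √21 = 4.6

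Blocks of 2 help. Blocks of 4 gain almost nothing over an unstratified 21:21 split, and blocks of 6 do worse.

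**Cost to the between-arm comparison.** Relative efficiency of 18 v 24 against 21 v 21 is 4·18·24/42² = 1728/1764 = 98%.

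**The case against.** The strongest reply is that block size, the number of age ranges and the handling of sparse cells normally belong to the full protocol, and that the percentages depend on them. This stands for the exact percentages. It does not rescue the claim, because equality fails at every block size tried. Blocks of 2 split each stratum as evenly as its count allows, and even then 21:21 occurs in fewer than a quarter of trials.

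A second reply is that randomisation follows baseline collection, which opens two weeks before the program, so a known cohort might be allocated in one batch with the odd families paired off. The text neither says this nor rules it out. The figures assume separate lists per stratum.

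A reader might also infer larger harms, which the documents do not support:

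- **The intervention arm falls short of its required number.** Section 2.7's minima are 18 for completion and 19 for acceptability and fidelity, counted in participants, and both parents of a family may attend. If the 42 are families and second parents count in addition, the arm falls below 19 parents in under 1% of simulated trials. Table 2 words acceptability by family, and section 2.7 does not settle the unit, so a shortfall cannot be asserted from the text.
- **Groups cannot be filled.** Section 2.4 needs only five members to start a group. With blocks of 2 or 4, intervention arms of fewer than 15 families were very rare (under 0.4%).
- **The trial comparison is compromised.** It is exploratory and adjusted for baseline score, and the efficiency loss is about 2% at 18 v 24.
- **The scheme is no better than simple randomisation.** It is better, on both arm size and factor balance.

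**Conclusion.** The point holds as one about a claim and a design choice. With at least 24 strata for about 42 families, section 2.3.2 does not ensure equal distribution between arms. The word is not ensured: a given trial may still end at or near 21:21. With blocks of 4 or more, the scheme gives up control of arm size for little or no gain in factor balance over an unstratified 21:21 split.

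The consequences are modest. The progression decisions rest on one-sample proportions against the Table 2 thresholds and are largely unaffected.

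The stratum count follows from the text alone. The percentages rest on 42 randomised families, full crossing of the four variables, separate lists per stratum, and the assumed shares and block sizes. Fewer families would make the strata sparser.

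**What to change.** Before the first randomisation, choose one of two schemes.

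1. **Fewer strata.** Stratify on one or at most two binary factors, for example one v both parents and a single age split, with small permuted blocks. With one binary factor and blocks of 4, the difference is at most 2 per stratum and 4 in all. At N = 42 its SD is 1.0 with blocks of 2 and 1.3 with blocks of 4. With two binary factors (4 strata) the bound is 4 × 1 = 4 for blocks of 2 and 4 × 2 = 8 for blocks of 4.
2. **Minimisation** with a random element over all four factors.

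In either case, enter the retained factors as covariates in the ANCOVA of section 2.8.1, which at present names only the pre-intervention score. Remove or restate the sentence in section 2.3.2 so that it claims no more than the scheme delivers.

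Cost: a new allocation list or a small minimisation program. Under the first option, dropped factors are balanced only by chance, and very small blocks are easier to predict. Under the second, adjusting for all four factors uses at least 1 + 1 + 2 + 1 = 5 degrees of freedom, which is noticeable but affordable with about 42 families.
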